#### The standard-of-care arm

The comparator arm corresponds to standard-of-care diagnostics currently provided to CAP patients at HUH. As described [19], this includes bacterial culture of respiratory tract samples and blood according to current guidelines (adapted from [20]). Blood culture isolates and relevant respiratory isolates are identified with matrix-assisted laser desorption/ionization time-of-flight mass spectrometry (MALDI-ToF MS) using the Bruker’s microflex LT instrument, MBT Compass software ver. 4.1 and Compass Library DB-8468 (Bruker Daltonics, MA, USA). Nasopharyngeal and/or oropharyngeal swabs are examined by an in-house real-time PCR test to detect respiratory viruses and atypical bacteria (influenza A and B, human parainfluenza viruses 1-3, respiratory syncytial virus, human metapneumovirus, rhinovirus, SARS-CoV-2, *Bordetella pertussis*, *Bordetella parapertussis*, *Mycoplasma pneumoniae* and *Chlamydia pneumoniae*). The total turn-around time for the in-house PCR test is up to 48 h and is comparable to other centres nationally. Standard methods also include the pneumococcal urine antigen test (Quidel Corporation, San Diego, USA). Any additional tests requested by the treating physician are noted and counted as part of standard methods. A positive SARS-CoV-2 result, growth in blood cultures and positive pneumococcal antigen test results are phoned to the treating staff.

#### *The FAP* plus *arm*

The FAP *plus* arm entails extended and rapid diagnostics on lower respiratory tract samples and telephonic feedback to treating staff with results. The feedback does not involve advice on treatment. All patients will receive the standard microbiological tests described above, with additional testing by the FAP *plus*. Through a feedback loop, both negative and positive FAP *plus* results are telephonically communicated to the treating staff.

### Criteria for discontinuing or modifying allocated interventions {11b}

A patient can withdraw from the study at any time at his/her own request. If the patient withdraws consent, the investigators may retain and continue to use any data collected and analysed before such a withdrawal of consent. If a patient withdraws from the study, samples collected and not tested will be destroyed and the investigator will document this in the study records.

### Strategies to improve adherence to interventions {11c}

Not applicable as the two interventions do not require patients to participate actively.

### Relevant concomitant care permitted or prohibited during the trial {11d}

Any additional microbiological methods introduced by the treating physicians are counted within the repertoire of standard diagnostic methods provided.

### Provisions for post-trial care {30}

Not applicable. The interventions do not involve active involvement or participation from the patients beyond providing informed consent as the trial is evaluating the utility of diagnostic tests used for diagnosing the aetiology in CAP, i.e., medical tests for determining the aetiology in CAP, and not treatments of CAP, are compared.

### Outcomes {12}

#### Primary outcomes

There are two primary outcome variables:Provision of pathogen-directed treatment based on a microbiological test result deemed as clinically relevant within 48 h of receipt of respiratory samples. This is a binary outcome variable taking on values as follows: yes, if such treatment was given to the patient, and no, if it was not given.Time (in hours) from receipt of respiratory samples to the patient receiving pathogen-directed treatment. This is a quantitative outcome variable recording the time elapsed from receipt of respiratory samples to provision of pathogen-directed treatment based on a microbiological test result deemed as clinically relevant (as defined in the first primary outcome) or an elapse of 48 h, whichever event came first. In other words, this outcome variable is subject to right censoring at 48 h. Right censoring could potentially occur for other reasons such as no aetiology being detected or the patient dying.

Since lack of microbiological identification is a major problem in CAP patients and enhancing rapid detection of significant pathogens could have a major impact on the clinical decision-making process, we selected two correlated primary outcomes with both time to and provision of pathogen-directed treatment. Limited evidence exists to support the use of these new molecular microbiological methods over standard of care, which uses standard microbiological testing. In a retrospective study including rapid molecular diagnostics, it has been suggested that de-escalation from broad-spectrum to pathogen-directed antibiotics could be undertaken in 77% of patients with CAP, while escalation should be done in 6%; however, a RCT is needed to confirm these findings [21].

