**Methods:**

Patients presenting to the emergency department of Haukeland University Hospital (HUH) in Bergen, Norway, will be screened for inclusion into a pragmatic randomised controlled trial (RCT). Eligible patients with a suspicion of CAP will be included and randomised to receive either standard-of-care methods (standard microbiological testing) or standard-of-care methods in addition to testing by the rapid and comprehensive real-time multiplex PCR panel, the BioFire® FilmArray® Pneumonia Panel *plus* (FAP *plus*) (bioMérieux S.A., Marcy-l’Etoile, France). The results of the FAP *plus* will be communicated directly to the treating staff within ~2 h of sampling.

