## Data collection and management

### Plans for assessment and collection of outcomes {18a}

Baseline information is collected by study nurses or investigating physicians through a structured interview in the emergency department. Symptoms and findings upon clinical examinations are recorded. Data pertaining to antimicrobial treatment and decisions, results from laboratory tests and medical imaging are obtained from electronic medical records and charts, after patient discharge, and used for the evaluation of the primary outcomes. For each patient, two experienced physicians separately evaluate the clinical relevance of all microbiological findings [19] and determine if and when the patient received pathogen-directed antimicrobial treatment based on a microbiological test result. In case of any inconsistency between the two physicians, a third independent physician will arbitrate. To be considered as pathogen-directed treatment, study physicians will note if (a) there is a change in antimicrobial treatment based on a microbiology test result or (b) a continuation of already correctly initiated antimicrobial treatment based on a microbiology test result, and (c) discontinuation of antimicrobial treatment based on negative microbiological test result(s). Empirical and pathogen-directed therapy will be determined using national guidelines recommended by the Norwegian Directorate of Health, data from national susceptibility reports, as well as results from anti-microbial susceptibility testing provided by the Department of Microbiology, HUH, as appropriate [25, 26]. Data will be registered in our eCRF (Viedoc). Data for the 30- and 90-day mortality, and 1- and 5-year mortality will be obtained from the Norwegian Cause of Death Registry.

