### Methods in analysis to handle protocol non-adherence and any statistical methods to handle missing data {20c}

As CAPNOR is a pragmatic trial, the main statistical analyses will be carried out according to the intention-to-treat principle using appropriate effectiveness estimands [40]. Specifically, for the two primary outcomes, which are based on an event time, possibly subject to right censoring, the statistical analysis will be based on all patients that were randomised. Likewise, for event-time-derived secondary outcomes, statistical analyses will also be based on the full set of randomised patients. For other outcomes, where missing values may occur, missing values will be imputed using outcome-specific imputation models unless complete-case or available-case analyses could be justified because the missing data mechanisms are missing completely at random or missing at random, respectively.

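### The time-to-treatment primary outcome permits right censoring because no aetiology was detected, with no censoring time given; applied before 48 h and earlier in one arm, this would bias the hazard ratio

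*Protocol article*

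**What the plan says.** The section on primary outcomes defines the second primary outcome as the hours from receipt of the respiratory sample to pathogen-directed treatment, or 48 h if that comes first: "In other words, this outcome variable is subject to right censoring at 48 h". The next sentence widens the rule: "Right censoring could potentially occur for other reasons such as no aetiology being detected or the patient dying". No time is attached to these further reasons.

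Other sections bear on this:

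- **Assessment of outcomes {18a}.** Pathogen-directed treatment includes "discontinuation of antimicrobial treatment based on negative microbiological test result(s". Status is determined from records after discharge by two physicians, with a third arbitrating.
- **The FAP plus arm.** "both negative and positive FAP *plus* results are telephonically communicated to the treating staff". The abstract says that results "will be communicated directly to the treating staff within ~2 h of sampling". Patients in this arm also receive all the standard tests.
- **The standard-of-care arm.** "The total turn-around time for the in-house PCR test is up to 48 h". Only certain positive results are listed as phoned.
- **Statistical methods {20a}.** A Cox or accelerated failure time model, or a similar event-time model.
- **Non-adherence and missing data {20c}.** For both primary outcomes, "the statistical analysis will be based on all patients that were randomised".
- **Blinding {17a}.** Outcome assessors and statisticians are not blinded.

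**The concern.** A Cox or accelerated failure time model assumes that a patient censored at time *t* has the same later chance of the event as comparable patients still under observation. A patient in whom no pathogen was found does not. The event must rest on a microbiological result, so failure to detect a pathogen lies between the test and the event and largely decides whether the event can occur. Censoring for that reason is informative.

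Detection is also what the intervention is meant to change. Taking such patients out of the risk set moves the comparison from all randomised patients towards patients with a detected pathogen, and that group differs by arm. Including every randomised patient in the analysis does not cure this, because inclusion does not fix when a patient leaves the risk set.

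The timing could differ by arm, since a panel result arrives within about 2 h and the in-house PCR can take up to 48 h. Because the protocol leaves the time open and assessors know the allocation, the choice could be made with allocation known. At stake is the hazard ratio of a primary outcome. An untreated patient with no aetiology is a plain no in the first primary outcome, but could leave the second before 48 h.

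**Working it through.** **1. The plan's own figures.** For the time outcome, n per arm = 2(z₀.₉₈₇₅ + z₀.₈₀)² / 0.2² = 2(2.241 + 0.842)² / 0.04 ≈ 475.2, so 476; the plan states 477. Then 954 / 0.9 = 1060, as stated. For the binary outcome, 50% v 40% with pooled variance gives 470 per arm, and 940 / 0.9 gives 1045 after rounding up, as stated. The sample size is not in dispute.

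**2. How many patients the rule could reach.** The sample-size section assumes that a pathogen is identified in 50% (FAP plus) and 40% (standard). On those figures, 50% and 60% of patients would have no aetiology.

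**3. Mechanism by hand.** Suppose there is no true difference: 40% have the event in each arm, with the same timing.
- Events per arm: 0.40 × 477 = 190.8. Non-events: 286.2.
- Assume 85% of non-events are labelled as no aetiology: 0.85 × 286.2 = 243.3. The other 42.9 stay to 48 h.
- Suppose the labelled patients leave by 4 h in the FAP plus arm, but not before 24 h in the standard arm. When half the events have occurred (95.4 remaining, at about 18 h), the risk sets are 95.4 + 42.9 = 138.3 and 95.4 + 286.2 = 381.6.
- Events occur at the same rate per hour in both arms, so the apparent hazard ratio at that point is 381.6 / 138.3 = 2.76, although the true value is 1.
- The Kaplan-Meier 48 h probability in the FAP plus arm becomes about 190.8 / (190.8 + 42.9) = 0.82, against a true 0.40.

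**4. Simulation.** Cox model with arm as the only covariate, 477 per arm, two-sided 0.025. The event-time shapes, the labelled share and the censoring times are assumptions; the documents give none of them.
- Set-up A: log-normal event times, median 18 h, log-SD 0.6, truncated at 48 h; 85% of non-events labelled; 800 to 1000 replicates where recorded. Ranges come from repeat runs.
- Set-up B: event times uniform on 2–48 h; all non-events labelled; 2000 replicates.

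| Truth | Censoring of no-aetiology patients, FAP plus v standard | A: HR, rejection | B: HR, rejection |
|---|---|---|---|
| 40% v 40% | none before 48 h | 1.00, about 3–4% | 1.00, 2.0% |
| 40% v 40% | 24–48 h in both | 1.00, 2.3% | 1.00, 2.4% |
| 40% v 40% | 12–36 h v 24–48 h | 1.30–1.31, 61–65% | not run |
| 40% v 40% | 12–24 h v 24–48 h | not run | 2.33, 100% |
| 40% v 40% | 2–24 h v 24–48 h | 1.92, 100% | not run |
| 40% v 40% | 2–4 h v 24–48 h | 2.66–2.68, 100% | 3.37, 100% |
| 50% v 40% | none before 48 h | 1.34, 78–80% | 1.35, 80% |
| 50% v 40% | 24–48 h in both | 1.34, 77–78% | 1.31, 70% |

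The bias comes from the gap in censoring times between arms. With late and equal times the false-positive rate stays near nominal. The remaining cost is some power: negligible in A, about ten percentage points in B.

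**5. The two definitions side by side.** Under {18a}, part (c), a patient with negative tests can still have the event, through a stop of antimicrobials. Under the primary-outcome text, the same negative tests may end that patient's time at risk. The sections do not say which comes first.

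**The case against.** The defence is substantial, and much of it stands.

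- **No early time is prescribed.** The sentence is hedged and gives no time, and the definition before it already assigns 48 h to an untreated patient. It can be read as explaining why some patients never have the event. On that reading there is no bias, and the two primary outcomes agree. This stands as a possible reading, but the sentence presents lack of aetiology as a reason other than the 48 h limit, so it does not settle the matter.
- **A 2–4 h censoring time fits the protocol poorly.** A reader might infer from the phoned negative panel that FAP plus patients are censored at about 2 h. The documents do not support that: the same cultures, in-house PCR and antigen test are done in both arms, so a final finding of no aetiology may come at similar, late times. The hazard ratio of about 2.7 is a worst case, not the plan's expected error.
- **A reader might also infer that a real benefit would be erased**, by dropping test-negative patients at the start. No section suggests this, and analysing all randomised patients runs against it.
- **A single patient is not both an event and censored.** Either antimicrobials are stopped on negative results or they are not. The tension with {18a} lies between the definitions, not within one patient's record.
- **Censoring at death** gives an ordinary cause-specific hazard, and its detail may sit in an analysis plan that is not shown. The documents give no 48 h death rate, so no size can be put on it.

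The defence does not remove the statement itself. The protocol names an informative reason for censoring within the definition of a primary outcome, so this is not mere silence left to an analysis plan.

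**Conclusion.** The point holds in conditional form. The primary-outcome text permits censoring for lack of aetiology besides the 48 h limit, gives no time for it, and sits awkwardly with the event definition in {18a}. Such censoring is informative for the planned models.

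If it is applied before 48 h and earlier in the FAP plus arm, the hazard ratio is biased upwards. Under the assumptions of set-up A with no true difference, it is about 1.3 with 61–65% false positives for a moderate gap (12–36 h v 24–48 h), and about 2.7 in the worst case. If it is late and equal in both arms, or only at 48 h, there is little or no bias.

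The documents do not show that the analysis is biased as planned. They leave open a choice that could decide a primary result, and that choice should be closed before analysis. The exact sizes rest on assumed event times, censoring times and the share of patients labelled as having no aetiology.

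**What to change.** Replace the sentence on other reasons for censoring with wording to this effect:

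> Patients who have not received pathogen-directed treatment remain at risk and event-free until 48 h after receipt of the respiratory sample, in both arms and whatever their test results, and are censored at 48 h. A patient who dies before 48 h without the event is held event-free at 48 h.

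Treating death before 48 h as a competing event is an acceptable alternative, if chosen in advance. Holding deaths event-free at 48 h makes the second outcome match a no in the first.

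Then align the primary-outcome text with {18a}: a stop of antimicrobials on negative results is an event at the time of the stop, and a patient with negative results and no such stop stays at risk to 48 h. Each patient then has one status at 48 h across both primary outcomes.

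The cost is a sentence or two in the outcome definition, repeated in the analysis plan. Treatment data are already taken from the medical records, so no new data are needed. The sample size of 1060 does not change.

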#### Secondary outcomes

There are 13 binary outcomes (encoded as yes/no):

Treatment with narrow-spectrum antibiotics within 48 h from study inclusionTreatment with a single dose of antibiotics onlyTreatment with antibiotics for not more than 48 h (within the first 7 days after inclusion)Treatment with intravenous antibiotics (within the first 7 days after inclusion)De-escalation from broad-spectrum to narrow-spectrum antibiotics (within the first 7 days after inclusion)Escalation from narrow-spectrum to broad-spectrum antibiotics (within the first 7 days after inclusion)Detected aetiology of CAP (within the first 7 days after inclusion)Provision of neuraminidase inhibitors to patients with diagnosed influenza (within the first 7 days after inclusion)Readmission within 30 days after dischargeDeath within 30 days, 90 days, 1 year and 5 years

There are eight quantitative outcomes:Duration of antibiotic use; intravenous and per-oral (in days)Duration of intravenous antibiotics (in days)Duration of broad-spectrum antibiotics (in days)Time from admission to time of pathogen-directed treatment (in hours)Time from admission to time of administration of antibiotic(s) (in hours)Time to appropriate use of isolation facilities (in days)Length of hospital stay (in days)Time from admission to a microbiological sputum test report (FAP *plus* result and/or sputum culture) (in hours)

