As CAP is a potentially serious infection, antibiotics are often given rapidly after presentation to hospital. Due to uncertain microbial aetiology, patients are initially treated with empirical antibiotics that cover a broad range of potential pathogens. The microbiological aetiology of CAP based on conventional routine microbiological testing is achieved in up to 30–40% of cases [12, 15]. With a few exceptions, standard-of-care diagnostic methods are too slow to influence early decisions on antimicrobial therapy. Culture-based techniques are also affected by prior use of antibiotics. Furthermore, sampling from the lower respiratory tract is problematic due to contamination and colonization from the upper respiratory tract flora. The management of CAP therefore largely relies on national empirical treatment guidelines that reflect the prevailing local epidemiology and microbial resistance profiles. Improving microbiological identification and enhancing rapid detection of significant pathogens could have a major impact on the decision-making process, by providing real-time information for treatment decisions within the emergency department. Rapid molecular testing for CAP aetiology may facilitate pathogen-directed treatment, reduce unnecessary antibiotic use, shorten length of hospital stay, improve viral detections and treatment and rationalize isolation facility use. However, limited evidence exists to support its use over standard-of-care microbiological testing. A recent randomised controlled trial (RCT) evaluated the use of molecular testing for respiratory viruses in hospitalized CAP patients in UK [16]. Molecular testing was associated with a greater proportion of patients being treated with brief courses of antibiotics, improved antiviral use, reduced length of stay and was considered safe. Moreover, respiratory viruses were detectable in up to 45% of hospitalized adults with acute respiratory illness [16]. These findings need confirming in other studies that include rapid molecular tests, targeting both viral and bacterial pathogens and with alternate outcome measures.

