Tests using multiplex real-time polymerase chain reaction (PCR) can reduce the time to results compared with standard PCR panels from 12 to 48 h to about 2 h, with the potential to direct initial antimicrobial choice. The new generation BioFire® FilmArray® Pneumonia Panel *plus* (FAP *plus*) (bioMérieux S.A., Marcy-l’Etoile, France) includes the automated detection of 27 relevant bacterial (including atypical bacteria) and viral respiratory pathogens together with seven antimicrobial resistance genes [17]. The assay requires a 2-min hands-on time and a run time of about 1 h. We hypothesize that utilizing the FAP *plus* panel in CAP patients can improve both the time to and the proportion of patients receiving pathogen-directed treatment, thereby shortening the exposure to unnecessary antibiotics and the length of hospital admission.

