## Statistical methods

### Statistical methods for primary and secondary outcomes {20a}

For the first primary outcome, which is a binary outcome capturing whether or not provision of pathogen-directed treatment was given, the comparison between arms will be performed using a logistic regression model. The difference between arms will be quantified by means of an odds ratio or as a difference in probabilities (“a risk difference”). For the second primary outcome, which is a quantitative outcome subject to right censoring capturing the time to pathogen-directed treatment was given, the comparison between arms will be carried out using a semi-parametric or fully parametric event-time model such as the Cox proportional hazards model or accelerated failure time model. Relevant covariate adjustment, including age and sex, will be included in both models.

Secondary outcomes will be analysed using the same two types of models as used for the two primary outcomes. However, for some quantitative secondary outcomes, there will be no right censoring present and, in such cases, linear models or linear mixed models will be fitted, depending on the absence or presence of repeated measurements.

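### Early death scores as a short antibiotic course, as no readmission and possibly as a short stay, so excess deaths in one arm would look like benefit in these secondary outcomes

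*Protocol article*

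**What the plan says.** **Outcomes.** In the Protocol article, Outcomes {12}, the secondary yes/no list includes treatment "with a single dose of antibiotics" only (no time window is printed), antibiotics for 48 h or less (assessed over the first 7 days), and 30-day readmission. Length of stay in days is among the quantitative outcomes. None of the four carries a condition on survival. Death at 30 days, 90 days, 1 year and 5 years stands as a separate outcome.

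**Direction of benefit.** Background and rationale {6a} expects the panel to improve targeted treatment, "thereby shortening the exposure to unnecessary antibiotics and the length of hospital admission". Among the positive results of a UK trial it reports: "Molecular testing was associated with a greater proportion of patients being treated with brief courses of antibiotics", together with reduced stay.

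**Analysis.** Section {20a} says: "Secondary outcomes will be analysed using the same two types of models" as for the primaries. That means logistic regression or an event-time model, with linear models where a quantitative outcome has no right censoring. It does not say which family length of stay belongs to. Death is named as a reason for censoring only under the second primary outcome: "Right censoring could potentially occur for other reasons such as no aetiology being detected or the patient dying". Section {20c} says that "missing values will be imputed using outcome-specific imputation models" unless a complete-case or available-case analysis can be justified. It mentions estimands in general terms and names no strategy for death.

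**The concern.** For the two short-course outcomes the literal wording gives a patient who dies early an observed yes. That value is not missing, so the imputation rule never reaches it, and a logistic model has no censoring to remove it. A patient who dies after discharge without returning gets an observed no on readmission. A stay ended by death enters a linear model as a short stay.

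This matters because the harm and the hoped-for benefit would point the same way. Under section {18a}, stopping antimicrobials after a negative result counts as pathogen-directed treatment. If some stopping or narrowing were harmful, the resulting early deaths would register as brief courses, short stays and avoided readmissions. Separate mortality outcomes would help a reader notice, but they do not correct the estimates for these four outcomes.

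**Working it through.** The article gives no figure for these outcomes and no 48 h, 7-day or 30-day mortality from the Norwegian cohort that it cites (8.9% at 1 year, 27.1% at 5 years). All rates below are therefore assumptions. Every scenario assumes no true effect among survivors. Arm size is 1060 / 2 = 530.

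**1. Short-course outcomes.** Let s be the short-course rate among survivors (equal in both arms) and d the probability of dying within 48 h while on antibiotics.

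- As worded: P(yes) = s(1 − d) + d, so the difference between arms is (d1 − d0)(1 − s).
- With death scored no: P(yes) = s(1 − d), so the difference is −s(d1 − d0).

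| s | early death | as worded | difference | death = no | difference |
|---|---|---|---|---|---|
| 5% | 1% vs 1% | 5.95% vs 5.95% | 0 | 4.95% vs 4.95% | 0 |
| 5% | 1% vs 3% | 5.95% vs 7.85% | +1.9 | 4.95% vs 4.85% | −0.1 |
| 20% | 1% vs 3% | 20.8% vs 22.4% | +1.6 | 19.8% vs 19.4% | −0.4 |
| 5% | 1% vs 5% | 5.95% vs 9.75% | +3.8 | 4.95% vs 4.75% | −0.2 |
| 20% | 1% vs 5% | 20.8% vs 24.0% | +3.2 | 19.8% vs 19.0% | −0.8 |

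At s = 5% and d = 3%, deaths make up 3 / 7.85 = 38% of the yes scores. With equal d the null stays null, and a true difference among survivors shrinks by the factor (1 − d). These figures let every such death score yes. That fits the 48 h outcome; for the single-dose outcome only deaths before a second dose count, so the effect there is smaller.

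**2. Readmission.** Let r be the readmission rate otherwise and d the probability of death after discharge before readmission, 3% vs 6%.

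- As worded, r(1 − d): at r = 10%, 9.7% vs 9.4% (−0.3 points, looks better); at r = 20%, 19.4% vs 18.8% (−0.6).
- Readmission or death, r(1 − d) + d: 12.7% vs 15.4% (+2.7, worse); 22.4% vs 24.8% (+2.4).

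**3. Length of stay.** This was simulated with 530 per arm and 100 runs. Latent stay was log-normal with a median of about 4 days, the same in both arms, and deaths fell between 0.3 and 4 days. Ranges run from deaths unrelated to prognosis to deaths concentrated in patients with longer latent stays.

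| nominal in-hospital death | linear model, difference in days | Cox, censored at death: HR for discharge | deaths kept as not discharged: HR |
|---|---|---|---|
| 3% vs 3% | about 0 | 1.00 | 1.00 |
| 3% vs 6% | −0.14 to −0.24 | 1.01 to 1.03 | 0.925 |
| 3% vs 10% | −0.25 to −0.52 | 1.01 to 1.09 | 0.84 to 0.86 |

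A linear model makes the arm with more deaths look better. Censoring at death removes most of that, but treats the dead as if they could still be discharged. Keeping them as not discharged shows the arm as worse.

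**The case against.** **It may be settled elsewhere.** The handling of death is often left to an analysis plan, this is a condensed article, and it never says that death is a success. That holds for modelling detail. But the outcome definitions, model families and imputation rule are fixed here, and the short-course definitions followed literally give the wrong score.

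**Size.** The illustrative rates may be high. A 3% death rate within 48 h is about a third of the 8.9% one-year figure, and the exclusion criteria remove patients expected to live less than 2 weeks. Halving the excess to 0.5% vs 1.5% gives 0.95 × 1 = 0.95 points. A real difference in early death would also show more clearly than the bias does. For 1% vs 3% with 530 per arm:

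- Spurious difference: SE = √[(0.0595 × 0.9405 + 0.0785 × 0.9215) / 530] = 1.56 points, so 1.9 / 1.56 = 1.2 SE.
- Early mortality: SE = √[(0.01 × 0.99 + 0.03 × 0.97) / 530] = 0.86 points, so 2.0 / 0.86 = 2.3 SE.

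This stands as a limit on severity, although the planned mortality outcomes start at 30 days, where later deaths add noise.

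**Stronger readings that the article does not support.** A reader might infer that the censoring and imputation rules aggravate the problem. They do not. Death is named as censoring only for the second primary outcome; if carried over to length of stay, censoring stops a death counting as a short stay, though the competing risk remains. Imputation does not touch observed values. A reader might also infer that in-hospital death counts as a favourable readmission result. It leaves that outcome undefined; the favourable no applies to deaths after discharge.

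**Conclusion.** The point holds for the definitions as printed. An early death is an observed yes on the two short-course outcomes. A death after discharge is a no on readmission. An in-hospital death shortens stay if a linear model is used, and length of stay is the weakest of the three because the article leaves its model open.

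Bias between arms needs unequal early mortality. For short courses it is then (1 − s) times the excess in early deaths, about 1.9 points at s = 5% and 1% vs 3%. With equal mortality there is dilution only. All rates are assumed, since the article gives none for the early period. Only secondary outcomes are affected. It should be corrected before analysis, and it does not threaten the primary comparison.

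**What to change.** In Outcomes {12}:

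- Score death within the outcome window as no for both short-course outcomes, and print a window for the single-dose outcome, which has none (the 7 days used for the 48 h outcome would serve).
- Add an analysis of readmission or death in all randomised patients, counting in-hospital deaths as events. Restricting it to patients discharged alive would condition on a post-randomisation event and lose those deaths.
- Analyse length of stay as time to discharge alive. Keep deaths as not discharged (a competing event), neither taken as short stays nor censored at death.
- Report mortality beside these outcomes.

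In section {20c}, state that values undefined because of death are not imputed.

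**Cost.** Wording and derivations. Section {18a} already plans to take mortality from the national registry. The downside is that the short-course and readmission outcomes then mix survival with antibiotic use or readmission, which is why mortality must be shown alongside.

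Replacing stay and antibiotic durations by days-alive outcomes is not needed. It would change the outcomes of a trial with 354 patients enrolled by February 2022, and may need post-discharge antibiotic data that the article does not show being collected.
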